##### Psychological Flexibility

The CompACT [48] is a 23-item self-report measure of psychological flexibility, allowing the calculation of subscale scores for (1) openness to experience, (2) behavioral awareness, and (3) valued action. Each item is presented on a 7-point Likert scale ranging from 0 (*strongly disagree*) to 6 (*strongly agree*). The CompACT has adequate internal consistency reliability (average interitem correlation, *r*=0.34), good convergent validity, and good discriminant validity [48]. Higher scores on CompACT indicate greater psychological flexibility.

#### Embedded Qualitative Interviews

We will purposively recruit 20-30 participants from the intervention group (ensuring a range of age, gender, cancer type, and website engagement) to participate in a semistructured interview 2-4 weeks after trial completion. Semistructured interviews will be used to allow flexibility in the focus of interviews for each participant [49], in-depth probing of individuals’ experiences using the FMW UK website, and factors that affect acceptability and engagement. Participants willing to take part in this embedded study will be offered the option to complete the interview in person (either at the university or in their own home) or via telephone or video call, provided the chosen interview mode adheres to any government and workplace COVID-19-related social distancing rules at the time. Any travel cost will be reimbursed. Our interview topic guide will probe for participants’ frequency of website use and, if applicable, reasons for low use, overall evaluation and perceived usefulness of the FMW program, and any suggestions for improvement, which are important components of acceptability and will be used to inform both refinements of the intervention materials and any planning for implementation after the trial is complete. All qualitative interviews will be audio-recorded and transcribed verbatim for later analysis.

### Analysis

The analysis plan matches the Australian FMW RCT [27] as closely as possible. Members of the research team involved in the analysis will be blinded to the condition allocation until the end of the trial. First, we will conduct data cleaning to ensure that all data values are possible and plausible. Errant data entries will be deleted from the final analysis data set and missing data will be handled using either prorating or imputation methods as is (1) appropriate to the collected data and (2) congruent with the specific scoring instructions for the psychometric measure from which there is a missing response.

Descriptive statistics will be used to provide sample characteristic information and to identify any potentially prognostic demographic or clinical covariates. Inferential statistical analyses are powered to undertake mixed model repeated measures analyses to examine intervention effects on change from baseline to follow-up for each outcome, using intention-to-treat analysis. Two models will be run for each: (1) unadjusted, accounting for covariance of baseline measures of outcomes and (2) fully adjusted, controlling for all potential confounding variables assessed. Where possible and adequately powered, we will include potential confounders in our analyses and evaluate the effects of missing data using sensitivity analysis. Cohen *d* effect sizes reflect intervention effects, and clinically significant changes will be assessed using reliable change indices. The health care use outcome will be summarized descriptively for activity counts and cumulative costs estimated by assigning unit costs to units of activity. Cost summaries are derived from discrete payer perspectives. Generalized linear models will be used to adjust for the same confounding variables as in the efficacy analysis. All quantitative data analyses will be undertaken in R software (R Foundation for Statistical Computing) [50] where possible, with any supplementary analyses conducted in IBM SPSS as appropriate*.*

Qualitative data collected during the embedded qualitative interviews will be analyzed using thematic analysis [51]. In accordance with best practice guidance for thematic analysis, analysis will be undertaken by one member of the local research team with a proportion audited independently by a second researcher. A small subgroup of the trial steering group will then be convened to review the preliminary thematic structure and provide feedback. Qualitative analysis will be performed using the NVivo software (QSR International).

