### Participants

#### Sample Size Calculation

Calculations were based on the primary outcome of change in cancer-specific distress between the two patient groups. The original FMW RCT sample size calculation [27] used a standardized effect size of 0.35 and an SD of 4 units, which equates to an absolute change in cancer distress scores of 1.4 units. This study observed a larger than expected SD and we propose a sample size based on a conservative estimate of the residual SD of 7 units accordingly (but keeping the clinically relevant difference at the aforementioned 1.4 units). The correlation between successive measurements on the same patient is assumed to be high, and so a conservative *r*=0.70 was used. Sample size calculations were performed assuming a paired two-tailed *t* test using the derived SD of the change in the primary outcome of 5.42. Assuming a patient attrition of 20% and α of .05, 294 patients (147 per study arm) are required for a statistical power of 80% [35]. We will allow up to 30% overrecruitment to mitigate the effects of missing data and to allow for at least minimal recruitment of less common cancer types.

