##### Psychological Impact of Cancer

The Psychological Impact of Cancer Scale [37] is a 12-item self-report measure of psychological adjustment to cancer. Each item is presented on a 4-point Likert scale anchored from 1 (*definitely does not apply to me*) to 4 (*definitely applied to me*). The Psychological Impact of Cancer Scale yields four subscale scores: cognitive distress, cognitive avoidance, emotional distress, and fighting spirit. Greater scores on each subscale indicate greater levels of the named construct (eg, a greater score on the Cognitive Distress subscale indicates greater levels of cognitive distress). The fighting spirit subscale will not be included because of underlying psychometric property issues [37]; the remaining three scales have reasonable internal consistency reliability (α≥.62) and good concurrent validity with longer measures of psychological adjustment to cancer [37].

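### The Analysis section says the trial is powered for each outcome, but the sample size was calculated for cancer-specific distress alone

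*Protocol article*

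**What the plan says.** Two sections of the protocol article describe what the sample size supports.

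- Analysis: "Inferential statistical analyses are powered to undertake mixed model repeated measures analyses to examine intervention effects on change from baseline to follow-up for each outcome", by intention to treat.
- Sample Size Calculation: "Calculations were based on the primary outcome of change in cancer-specific distress between the two patient groups". The inputs that follow all concern that one outcome: "keeping the clinically relevant difference at the aforementioned 1.4 units", "a conservative estimate of the residual SD of 7 units accordingly", "so a conservative *r*=0.70 was used", and a t test run "using the derived SD of the change in the primary outcome of 5.42". The test is named in the sentence beginning "Sample size calculations were performed assuming a paired two-tailed". With 20% attrition, α of .05 and 80% power, the result is 294 patients, 147 per arm. Up to 30% over-recruitment is allowed.

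The Secondary Outcomes section describes the DASS-21 subscales, the QLQ-C30 global and functional scores, three Psychological Impact of Cancer subscales and the cost questionnaire. It gives their scoring and measurement properties, but no difference to detect, SD of change or power for any of them.

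The Background reports that the larger Australian trial did not reproduce the earlier between-group differences, but found better emotional functioning and lower health care use in the intervention arm. The Objective is to test whether outcome effects are replicated or improved.

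**The concern.** Taken at face value, the Analysis sentence gives the whole outcome set a property that was worked out for one member of it. Adequate power for distress would say nothing about a score with a different SD, a different correlation with baseline or a different plausible effect.

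The point matters here because this is a replication trial and the Australian between-group effects are secondary outcomes in it. If the report repeats that the analyses were powered for each outcome, a null result on emotional functioning could be read as failed replication, when the design may simply have been too small to show an effect of that size.

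**Working it through.** **1. Reproduce the stated sample size** (all inputs from Sample Size Calculation).

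- SD of change = 7 × √(2 × (1 − 0.70)) = 5.42, as stated. This treats 7 as the SD at a single time point.
- Paired formula, normal approximation: n = (5.42 × (1.960 + 0.842) / 1.4)² = 117.6.
- Attrition: 117.6 / 0.80 = 147.05, i.e. 147. This is taken per arm, giving 294.

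The figure reproduces from the distress inputs alone. No secondary outcome enters it.

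**2. What 147 per arm gives for the primary between-arm comparison.** Completers per arm: 147 × 0.80 = 117.6, taken as 118.

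- Unadjusted change scores: SE = 5.42 × √(2/118) = 0.706; 1.4 / 0.706 = 1.98; power = Φ(1.98 − 1.96), about 51%.
- Baseline-adjusted: residual SD = 7 × √(1 − 0.70²) = 5.00; SE = 5.00 × √(2/118) = 0.651; 1.4 / 0.651 = 2.15; power = Φ(2.15 − 1.96), about 58%.
- Baseline-adjusted at full over-recruitment: 147 × 1.3 × 0.80 = 152.9 completers, about 153 per arm; power about 69%.

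The paired formula yields the number needed for a within-group change, so using it as a per-arm size does not give 80% between arms. For a between-arm comparison of change scores, 80% needs 236 completers per arm, or 295 per arm after attrition.

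**3. What the same numbers can detect on a secondary score.** In SD units of the score at one time point, for a baseline-adjusted comparison at one follow-up:

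d = (1.960 + 0.842) × √(1 − r²) × √(2/m), with m completers per arm.

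| Baseline correlation r | m = 118 | m = 153 (full over-recruitment) |
|---|---|---|
| 0.7 | 0.26 | 0.23 |
| 0.5 | 0.32 | 0.28 |
| 0.3 | 0.35 | 0.31 |

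The value 0.7 is the article's assumption for distress. Its use for other scores, and the values 0.5 and 0.3, are assumptions made here.

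**4. Power at the trial's own standardized target.** The primary target is 1.4 / 7 = 0.20 SD. For a secondary score with a true effect of that size and m = 118, power is about 58% (r = 0.7), 43% (r = 0.5) or 36% (r = 0.3). So 80% power does not carry over to the secondary scores even at the standardized effect that the trial sets for itself.

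**The case against.** The strongest reply is that the sentence loosely describes which model is run for each outcome, and that the article tells the reader the true scope elsewhere. Sample Size Calculation opens by naming the primary outcome, primary and secondary outcomes have separate headings, and Cohen d and reliable change indices are planned alongside significance tests. That reading is possible, and it makes this a wording fault rather than a design error. It does not rescue the sentence, which says the analyses are powered and extends this to every outcome. Nor does a fuller protocol or analysis plan answer it, because the article itself makes the claim.

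Three further points stand in part:

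- **Health care use.** It is to be summarized descriptively, with generalized linear models for adjustment, so it is not plainly covered by the repeated-measures claim. Of the two Australian effects, the claim bears most directly on emotional functioning.
- **Over-recruitment.** The 30% allowance improves the detectable range and is shown above. It is a ceiling and not a commitment, so both columns are needed.
- **Repeated measures.** A mixed model that draws on several follow-ups could do better than a single contrast. The article gives no inputs from which to compute that.

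A reader might infer that the trial intends to treat secondary results as confirmatory, or a null secondary result as proof of no effect. The article says neither. A reader might also turn this into a multiplicity complaint, but error control across secondary outcomes is a separate matter, commonly left to the analysis plan. The article sets no rule that all secondary scores must reach significance.

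**Conclusion.** The claim of power for each outcome is wrong as written. The sample size rests on cancer-specific distress alone, and the documents support no power figure for any secondary score. This conclusion needs only the two sections read side by side.

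The size of the gap depends on assumptions: a single follow-up contrast, baseline adjustment, 20% attrition and, for correlations other than 0.7, values the article does not give. On those terms, secondary differences smaller than roughly a quarter to a third of an SD would not be detected with 80% power. Limiting the sentence to the primary outcome is not enough by itself, because the primary's own 80% does not hold for the between-arm comparison.

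Misreading of null secondary results is a risk that the wording creates, and not something the plan states it will do.

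**What to change.** Change the wording in three places.

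- **Analysis, power sentence.** Say that the sample size addresses the primary outcome only, and that the mixed models are also applied to the secondary outcomes without a power calculation for them.
- **Power of the primary comparison.** Restate it for the between-arm contrast to be reported. With the article's inputs and a baseline-adjusted single follow-up this is about 58% at 118 completers per arm. If the repeated-measures model is expected to do better, give the inputs and the resulting figure.
- **Secondary scores.** State the difference detectable with 80% power (about 0.26 to 0.35 SD at 118 completers per arm, 0.23 to 0.31 SD at full over-recruitment) with its assumptions. Report these scores as estimates with confidence intervals, so that a null result can be judged by the effects it leaves open.

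Naming a key secondary outcome is a design choice and is not needed for this correction.

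The cost is that the stated power becomes less favourable. These changes alter no patients and no data.

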### Data Sharing Plan

As part of our commitment to transparent open science practices, anonymized quantitative data sets generated from the trial will be stored and made available through the Open Science Framework following the publication of trial findings. These data will include the primary and secondary outcome measures, demographic and clinical data, and any moderating or mediating variables that we ultimately include in all planned and exploratory analyses. We will not include the name of the participants’ recruiting cancer centers in the interest of maintaining participant anonymity. Participants will be asked to explicitly consent for their anonymized data to be shared with other members of the research community in this way.

Given the focused nature of the qualitative interview schedule (ie, engagement with, views on, and suggestions for improving FMW UK), and the ethical risks involved in releasing qualitative data openly because of the difficulties in adequately deidentifying data, we do not currently plan to share data from this aspect of the trial. However, we will review best practice guidelines as they change over the course of the project and review this aspect of the data sharing policy at the time of project completion.

### Monitoring of Adverse Events

We have risk-assessed the potential for serious adverse events from this clinical trial to be low. When a member of the research team is contacted by a participant reporting an adverse event (including elevated psychological distress), they will follow a standard protocol to assess the seriousness of the situation. In the case of disclosure of suicidality and immediate safety concerns, the researcher will contact emergency services and remain on the telephone with the participant until they arrive. In all other cases, the researcher will provide signposting to additional psychological support available as part of standard care, including to the general practitioner and clinical team. All adverse events will be reported to the principal investigator who will assess the severity of the event and report it to the study sponsor (and NHS Research Ethics Committee in the case of a serious adverse event). Provided that participants have provided consent for us to do so, we will also report the adverse event to the clinical team so that a member of the relevant care team can contact the participant to ensure that appropriate support is put into place.

### Ethical Approval and Trial Registration

Ethical review was sought from the University of Chester Department of Psychology Ethics Committee to trigger agreement from the university to act as study sponsor. Full approval was obtained from the NHS Research Ethics Committee (reference: 21/WA/0029), leading to the approval of the Health Research Authority, followed by site-specific research governance approvals at each site. As one of our sites is in Wales, professional Welsh translations of study information are being provided for use at that site, in accordance with the Welsh Language Act (1993) [52]. The trial was registered on the ISRCTN (International Standard Randomized Controlled Trial Number; reference: ISRCTN14317248; date registered 08/04/2021). We have established a trial profile on the Open Science Framework (DOI 10.17605/OSF.IO/ZSHBQ; date registered: May 18, 2021) to facilitate the later sharing of data. The trial was designed in accordance with the principles for medical research involving human subjects, as laid down in the World Medical Association Declaration of Helsinki.

## Results

The grant for this trial was awarded by the North West Cancer Research in September 2019. The project commenced in April 2020, but the initial progress was slower than expected because of the impact of the COVID-19 pandemic on health research in the United Kingdom [53].

### User Testing of the Adapted FMW Program

All intervention adaptation work was completed by January 2021. User feedback from our panel of three health care professionals and four cancer survivor volunteers was then collated. The overall response was positive, with health care professionals noting that the program was helpful and supportive and that they would recommend it to their patients. The cancer survivors also praised the program, stating that they wished they had had access to something similar during treatment. Some minor changes were recommended, as summarized below.

First, a number of technical issues were highlighted and corrected, including the following:

The website tutorial and resources tab were made to be more prominently visible through altered placement and graphical appearance on the webpage.Some navigational issues were also highlighted, with some links not working and others navigating to the wrong page.The embedded YouTube videos were set up as playlists, which means that each one, on completion, linked to the next video in the playlist, giving a preview to what was to come in other modules. YouTube has the option to easily disable this feature.The linked content was reprogrammed to launch in a new tab to prevent users from becoming lost in the underlying web architecture.

Second, user feedback highlighted some areas where content could be more inclusive. For example, some occurrences of gendered language were replaced with more inclusive language (they or them), and the skin tone of some cartoon images was varied to represent the population diversity of our target recruitment area. Minor changes were made to correct a perceived bias toward breast cancer and to be more inclusive of those without a faith belief or religion.

Third, some aspects of terminology were perceived as outdated (eg, *taking the telephone off the hook*) and were thus replaced (eg, *turning your mobile off*). Similarly, recommendations for meeting new people and maintaining social support were updated to reflect the drive toward social media over traditional media. Some minor changes were made to the language used to refer to different types of health care professionals used in the UK health care system.

Finally, changes were recommended to the flow of the *Improving Communication* page and a greater range of linked or recommended charities and support organizations were added to the support pages. One participant recommended changes to the *Sexuality and Intimacy* section related to safe sex practices during cancer treatment, which were then researched and rewritten by our team to align with current NHS guidance [54].

### Clinical Trial Progress

We launched recruitment for the clinical trial in late April 2021, initially at our two largest hospital centers. The remaining sites will begin recruiting from the summer of 2021. We plan to complete recruitment by February 2022, with all follow-up quantitative data collection completed by October 2022 and all qualitative interviews completed by December 2022. Data analysis will then take place. We aim to report on the findings from the trial from spring 2023.

## Discussion

### Trial Status

The FMW program of psychological support has yielded promising results among recently diagnosed adult cancer survivors in Australia [25-27]. However, the adaptation work described in this protocol was necessary to make this program suitable for implementation in the United Kingdom. Including equipment, web design, videography, and patient and public reimbursement, our adaptation work has costed in the region of £25,000 (US $34,593; excluding staffing costs), taking approximately 10 months to complete. This was a considerable undertaking but still represents a very substantial cost saving compared with developing a new intervention from scratch [55,56]. These efforts were important and justified, given the positive feedback reported by our user testing group. Importantly, our approach to adaptation of the website content allowed us to adopt some elements of co-design with patient experts [57], as recommended by the UK NIHR [58]. This approach to close—and *active*—partnership work with our broader expert stakeholders will not only increase the acceptability of our adaptation [59] but will also enhance the possibility for later implementation and impact [60] across the United Kingdom, should this trial demonstrate efficacy.

The FMW UK clinical trial, which is now underway, will test the efficacy of this program in reducing cancer-specific distress, improving well-being, and reducing the need for broader health care use. As much as possible, we retained (or improved) features of the original Australian RCT to ensure that our work can act as a replication trial. Replication studies are an important aspect of the scientific process [61] and have an important place in psychological [62], broader health sciences [63], and clinical trials [64] literature. Our mixed methods design is important to the integrity of our trial and offers not only efficacy and cost-effectiveness information but also information on the sociocultural context and lived experiences of participants engaged in the intervention [65].

If our UK-based trial does indeed replicate the Australian findings, then this research study will have identified a novel and cost-effective method of psychosocial care delivery for cancer survivors in the NHS. This will of course be limited to those particular sites from which we are recruiting (ie, in North West England and North Wales), and so some additional work may need to be undertaken to explore potential barriers and appropriate pathways for rapid implementation and evaluation across other parts of the United Kingdom.

